### Interim analyses {21b}

Per protocol, no interim analyses will be performed.

### Methods for additional analyses (e.g., subgroup analyses) {20b}

Subset analyses will be performed for surgical variables such as recurrent surgery, tumor type (hormonal balance), size, and position (Wilson-Hardy classification, Knosp classification). Demographic variables including patient age, gender, body mass index, medication use, comorbidity, and smoking habits are also analyzed. The data will be statistically tested using a simple *t*-test or Mann–Whitney *U* test, or Fisher’s exact test or chi-squared test depending on normality, type of variable, and number of events. We do not intend to perform adjusted analyses.

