### Outcomes {12}

The primary end point is the success rate of both techniques at 3 months postoperative, which means the absence of CSF leak that needs surgical revision or any other intervention e.g., lumbar drainage, repeat imaging, or longer hospitalization. Success rate in both groups will be reported in proportions with a 95% confidence interval.

Secondary endpoints include identification of potential risk factors for reconstruction failure, assessment of potential interference of reconstruction material with post-operative imaging, analysis of the effect of the treatment on quality of life (QoL), and post-operative rhinological symptoms. Rhinological symptoms are assessed based on specific validated questionnaires, i.e. visual analog scale (VAS) (for runny nose, nasal itches, sneezing, nasal congestion, facial pain, headache, loss of smell), Sino-Nasal Outcome Test-22 (SNOT-22) and Skull Base Inventory (SBI).

The outcomes will be assessed at six study visits within a time frame of 1 year (Table 2), and a comparison will be made between the two groups considering the change to baseline (preoperative visit). Data will be presented as mean and standard deviation or median and interquartile range for continuous variables (including VAS score, SBI score, SNOT-22 score) or as proportions with 95% confidence intervals for categorical variables (intraoperative leak, complications, surgical indication, or type of tumor).

**Table 2 Tab2:** Outcome assessment

**Procedure**	**Visit 1** *Screening*	**Visit 2** *Allocation*	**Visit 3** *FU1*^a^	**Visit 4** *FU 2*^b^	**Visit 5** *FU 3*^c^	**Visit 6** *FU 4*^d^

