### Sample size {14}

Sample size calculation was performed according to the primary outcome, using an online power calculator for binary outcome non-inferiority trials (Sealed Envelope Ltd. Available from: https://www.sealedenvelope.com). This is a non-inferiority trial with a binary outcome using a one-sided alpha 0.05 and 80% power. The assumed success rate is 94.3% in the control arm, based on center-specific experience as well as the literature [14]. Data on the use of L-PRF for this indication is limited, but we assume a 95% success rate based on prior feasibility studies [8–10].

The statistical hypothesis for testing the treatment difference is presented as follows; H_0_: Δ ≤  − 0.07 tested against the alternative hypothesis H_A_: Δ >  − 0.07, where Δ is the difference between the success rates of experimental and control condition and − 0.07 is the non-inferiority difference. The non-inferiority limit was set at 0.07 considering (a) reported CSF leakage rates without commercially available fibrin sealant averaging 17.2% [15] and (b) important additional benefits of L-PRF compared to commercially available fibrin sealants including the completely autologous nature (eliminating immune reactions), presence of immunologic cells and reduced costs.

Based on this power calculation, 212 patients need to be included, 106 in each group. In order to account for potential missing follow-up information, failure of L-PRF preparation, or non-adherence to the allocation (expected drop-out rate less than 2%), 220 subjects will be enrolled, 110 in each group.

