## Statistical methods

### Statistical methods for primary and secondary outcomes {20a}

Data will be analyzed in GraphPad Prism software using a simple *t*-test, or nonparametric Mann–Whitney *U* test when not normally distributed, with Bonferroni Holm correction for multiple testing. A *p*-value ˂0.05 is considered statistically significant. The primary outcome, i.e., CSF leakage, will be analyzed in terms of a difference in risk between the two treatment groups. The mean difference between the two treatment groups will be reported as a 95% confidence interval. Secondary endpoints are calculated using simple *t*-test, or nonparametric Mann–Whitney *U* test when not normally distributed, or Fisher’s exact test or chi-squared test, based on the number of events.

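### If the planned subset tests compare the arms, none of them tests whether the L-PRF effect differs between subsets, and for leaks they ignore the -0.07 limit

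*Protocol article*

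**What the plan says.** The section on additional analyses {20b}, whose heading gives subgroup analyses as its example, states: "Subset analyses will be performed for surgical variables such as recurrent surgery, tumor type (hormonal balance), size, and position". It continues: "Demographic variables including patient age, gender, body mass index, medication use, comorbidity, and smoking habits are also analyzed". The tests named are a simple t-test or Mann-Whitney U test, or "Fisher’s exact test or chi-squared test depending on normality, type of variable, and number of events". It ends: "We do not intend to perform adjusted analyses".

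Three other places bear on this:

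- Statistical methods {20a}: a p-value below 0.05 "is considered statistically significant", and the t-test and Mann-Whitney test are to be used "with Bonferroni Holm correction for multiple testing". The family of tests for that correction is not defined, and it is not repeated for the subsets.
- Outcomes {12}: one secondary endpoint is "identification of potential risk factors for reconstruction failure", which the same variables could also serve.
- Sample size {14}: "This is a non-inferiority trial with a binary outcome using a one-sided alpha 0.05 and 80% power". The margin there is -0.07 on the difference in success rates.

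No treatment-by-subset interaction or homogeneity test is named, and no subset sizes are given.

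**The concern.** A subgroup analysis in a randomised trial is meant to ask whether the treatment effect differs between kinds of patient. A two-sample test run separately in each subset does not answer that. It asks whether there is an effect in this subset, and the answer depends heavily on how many patients or events the subset holds. Two subsets with the same true effect can easily fall on opposite sides of 0.05.

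For leaks there is a second problem. The trial is built to exclude a loss of 7 points or more, but Fisher's and chi-squared tests take equality as the null hypothesis. A large p-value in, say, recurrent surgery can be taken to mean that L-PRF is as good there, although the -0.07 limit was never examined and the test had little chance of detecting a loss of that size.

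At stake is how subset results are read, not the primary conclusion. The Discussion expects the trial to inform future reconstruction decisions, and the listed surgical variables are the sort of features by which readers may look for different answers.

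**Working it through.** **Inputs from Sample size {14}.** Control success 94.3% (leaks 5.7%), L-PRF success 95% (leaks 5.0%), margin 0.07, one-sided alpha 0.05, power 80%, 106 per arm needed, 110 per arm enrolled. The 17.2% leak rate without sealant is used only as a large-effect scenario.

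**The plan's own figure.** n per arm = (1.645 + 0.842)² × (0.943 × 0.057 + 0.95 × 0.05) / (0.07 + 0.007)² = 6.18 × 0.10125 / 0.00593 ≈ 105.6, so 106 per arm and 212 in total. This reproduces.

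**Assumption.** Because no subset sizes are given, take two equal halves of the 220 patients, 55 per arm in each, with the same true effect in both. If one half reaches p < 0.05 with probability p, exactly one of the two halves does so with probability 2p(1 − p).

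**Leaks.** Probability of p < 0.05 in one half, by full enumeration of the two binomial distributions (two-sided 0.05, 55 per arm):

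| True leak rates | Fisher | Exactly one half significant | Chi-squared | Exactly one half significant |
|---|---|---|---|---|
| 5.0% v 5.0% | 0.009 | 1.8% | 0.045 | 8.6% |
| 5.7% v 5.0% (planned) | 0.011 | 2.2% | 0.048 | 9.1% |
| 5.7% v 12.7% (full margin worse) | 0.137 | 24% | 0.242 | 37% |
| 5.7% v 17.2% | 0.353 | 46% | 0.485 | 50% |

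- With 30 per arm, Fisher's power against 5.7% v 12.7% falls to 0.042.
- If L-PRF were worse by the full margin in both halves, both Fisher tests would still be non-significant with probability (1 − 0.137)² ≈ 0.74.
- The 90% interval for the risk difference in one half has a half-width of about 1.645 × √(2 × 0.057 × 0.943 / 55) = 0.073, slightly wider than the margin itself.
- Expected leaks at the planned rates: 110 × 0.057 + 110 × 0.050 = 11.8, about 12 in the whole trial.

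**Scores (VAS, SNOT-22, SBI).** The article gives no effect size, so assume one with 80% two-sided power overall: d = (1.960 + 0.842) × √(2/110) = 0.378 SD.

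- Power in one half: Φ(2.802/√2 − 1.960) = Φ(0.021) = 0.508.
- Exactly one half significant: 2 × 0.508 × 0.492 = 0.50.
- With 30/70 and 20/80 splits the figure is 55% and 61%. With 90% overall power and equal halves it is 47%. With no true effect it is 2 × 0.05 × 0.95 = 9.5%.

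An interaction test at 5% would hold the false finding of a difference between subsets at about 5% in all of these cases.

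**The case against.** The strongest reply is that the section never says the arms are compared within subsets. Choosing a test by the type of variable fits a comparison of age, body mass index or smoking between patients with and without a leak, which is the risk-factor endpoint. This stands as a real ambiguity, and it is why the point is conditional. But the heading names subgroup analyses, and risk factors are listed separately under Outcomes {12}, so comparing the arms is the natural reading.

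A second reply is that interaction tests and exploratory labels belong in an analysis plan. Their absence alone would be no finding. Here, however, the article goes further: it names the tests and adds that no adjusted analyses are intended, so the method itself can be judged.

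Three stronger readings are tempting, and the documents do not support them:

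- *That contradictory subset results arise half the time in this trial.* The 50% needs a score effect with about 80% overall power. For leaks at the planned rates and with the named tests it is 2 to 9%.
- *That an interaction test is forbidden.* Covariate adjustment and testing effect modification are different things, and an exact homogeneity test needs no adjusted model. The article only fails to name one.
- *That false subset claims will be made, from uncorrected tests.* Nothing says how subset results will be used, and the Discussion's remark on future decisions concerns the trial as a whole. A Holm correction is named, though its reach is unclear. If it does not reach the subsets, about 10 independent tests at 0.05 carry a 1 − 0.95¹⁰ = 40% chance of at least one false positive. If it does, it still does not compare effects between subsets, and it lowers the power for leaks further.

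Finally, an interaction test on about 12 leaks is itself very weak. That is true, and the fix must guard against over-reading it.

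**Conclusion.** The point holds in a limited form. As written, the subset methods cannot show whether the effect of L-PRF differs between subsets, and for leaks they test a hypothesis other than the trial's own. With equal halves, Fisher's test would miss a loss of the full margin about 86% of the time (power 14%; 4% with 30 per arm), so a non-significant subset must not be read as non-inferior. For scores, one significant half and one non-significant half would occur in about 50% of trials with a common effect, provided that effect has 80% power overall. For leaks at the planned rates the likelier misreading is the opposite one: no significance in any subset, taken as reassurance everywhere.

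These sizes rest on assumed equal halves and, for the scores, an assumed effect. The conclusion also rests on reading the section as a comparison of the arms within subsets. The primary analysis is not affected. The change should be made because the better method is cheap.

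**What to change.** In the section on additional analyses {20b}, or in the analysis plan with a matching correction there:

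1. State for each listed variable whether it serves the risk-factor endpoint, effect modification, or both.
2. For effect modification, replace within-subset p-values by the risk difference (leaks) or mean difference (scores) with its confidence interval in each subset, and show the leak results against -0.07.
3. Add one treatment-by-subset test per pre-listed factor: a linear model with an interaction term for scores, and an exact homogeneity test or an exact or Firth logistic interaction for leaks. State that the exclusion of adjusted analyses does not cover it.
4. Label all of this exploratory, and allow no claim from a within-subset p-value or from a non-significant interaction.

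The cost is new wording, slightly more analysis work and possibly different software output. No extra patients or data are needed. The drawbacks are fewer subset claims and an interaction test for leaks that will have low power with about 12 events expected.

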## Background and rationale {6a}

The endoscopic endonasal transsphenoidal approach (EETA) to the skull base is a minimally invasive surgical technique that is used to treat a wide range of conditions affecting the skull base, such as pituitary tumors, suprasellar tumors and other diseases of the skull base. EETA is performed through the nasal cavity, without the need for an open craniotomy or facial incision, which leads to a faster recovery, reduced postoperative pain, and a lower risk of complications. However, the nasal cavity is a delicate and complex area that requires precise surgical techniques and can be susceptible to bleeding and inflammation. Additionally, recent advancements in endoscopic endonasal approaches (EEA) for skull base lesions have resulted in a significant increase in the extent and complexity of skull base defects, demanding more elaborate and novel reconstruction techniques to improve healing and prevent reconstruction failure. One major complication of EETA is postoperative cerebrospinal fluid (CSF) leakage. Our recently published systematic review, summarizing data from 113 studies, showed an average postoperative CSF leakage rate of 4.1% in endoscopic transsphenoidal surgeries [2]. A well-known risk factor for postoperative CSF leak is the presence of intraoperative leakage, in case of malignancy or, in cases where a thinned arachnoid herniates into the sella. As the pituitary is located in the diaphragma sellae, a double fold of the dura, large tumors may extend through the central opening of the diaphragm, resulting in a typical dumbbell shape, with an increased risk of CSF leak.

Postoperative leaks may require revision surgeries and/or external CSF drainage. Adequate dural closure is necessary to prevent CSF leak-related complications such as infections and intracranial hypotension. Currently, commercially available fibrin sealants, including Tisseel® and Tachosil®, are considered the gold standard for reinforcement of dural closure, due to their hemostatic, adhesive, and sealant properties [3]. However, problems regarding efficacy, cost, and safety have been reported [4, 5]. As such, commercially available fibrin sealants are expensive and may risk inducing hypersensitivity reactions.

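### Risk factors for reconstruction failure get only one-at-a-time significance tests on about 12 expected failures; exploratory odds ratios with intervals would serve this secondary endpoint better

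*Protocol article*

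**What the plan says.** The Outcomes section of the Protocol article states: "Secondary endpoints include identification of potential risk factors for reconstruction failure". The abstract and the Discussion repeat this aim.

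The section on statistical methods for primary and secondary outcomes analyses secondary endpoints by t-test, Mann-Whitney, Fisher or chi-squared test. The threshold is p < 0.05, and the t-test and Mann-Whitney analyses come "with Bonferroni Holm correction for multiple testing".

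The section on additional analyses names at least ten variables. Four are surgical (recurrent surgery, tumour type, size, position) and six are demographic or clinical (age, gender, body mass index, medication, comorbidity, smoking). It assigns them the same tests and closes: "We do not intend to perform adjusted analyses".

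The Background describes a linked mechanism: "large tumors may extend through the central opening of the diaphragm, resulting in a typical dumbbell shape, with an increased risk of CSF leak". It also calls intra-operative leakage a well-known risk factor. That leak is recorded (Outcomes section and its assessment table), but the list of variables in the additional-analyses section does not name it.

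**The concern.** The trial was sized for the non-inferiority comparison, and failures are meant to be rare. A significance test of one factor against so few failures will usually miss a factor that doubles or triples the odds. A p-value above 0.05, without an effect estimate, does not show the reader how little was learned.

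Separate tests also cannot say which of several related factors carries the risk. By the Background's own account, large tumours are the ones that extend upwards, so size and position overlap. If both are flagged, or only one, univariable tests give no means of telling them apart.

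At stake is how this one secondary endpoint is read: a list of non-significant factors could be taken as reassurance, and a flagged factor as a cause when it is only a marker.

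**Working it through.** **Inputs from the Sample size section.** "The assumed success rate is 94.3% in the control arm"; "we assume a 95% success rate based on prior feasibility studies"; 106 per arm evaluable, 110 per arm enrolled; "The non-inferiority limit was set at 0.07"; one-sided alpha 0.05, power 80%.

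**Reproducing the plan's own figure.** With unpooled variance,

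n per arm = (1.645 + 0.842)² × (0.943×0.057 + 0.95×0.05) / (0.95 − 0.943 + 0.07)² = 6.18 × 0.10125 / 0.00593 ≈ 105.6, so 106.

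This matches, so the two rates are the ones the plan was built on.

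**Expected failures.** 110×0.057 + 110×0.05 = 6.27 + 5.50 = 11.8 of 220, or 5.35% overall. The 95% binomial range is 6 to 19. With 212 patients it is 11.3. At the 4.1% leak rate quoted in the Background it would be 220×0.041 = 9.0. Against ten listed factors this is about 11.8/10 = 1.2 failures per factor.

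**Power of Fisher's exact test.** Two-sided, N = 220, overall failure 5.35%, computed by summing over all binomial outcomes. Prevalences and odds ratios are assumptions. The 0.005 column is the first Holm step if the family were ten tests (0.05/10), also an assumption.

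| Factor present in | Odds ratio | Failure risk with / without factor | Power at 0.05 | Power at 0.005 |
|---|---|---|---|---|
| 30% | 2 | 8.1% / 4.2% | 18% | 4% |
| 30% | 3 | 9.7% / 3.5% | 40% | 15% |
| 30% | 5 | 11.8% / 2.6% | 70% | 41% |
| 50% | 2 | 7.1% / 3.7% | 13% | 2% |
| 50% | 3 | 7.9% / 2.8% | 29% | 6% |
| 50% | 5 | 8.8% / 1.9% | 54% | 18% |

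**Continuous factors.** With 12 failures against 208 non-failures, a t-test at 0.05 needs a difference of about 0.84 SD for 80% power. Power for 0.5 SD is 39%.

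**What a non-significant result would look like.** Take 12 failures and a factor in 66 of 220 patients (30%).

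- If 7 of the 12 failures have the factor, the odds ratio is 3.5 and Fisher's p is 0.047, just significant.
- If 6 of the 12 have it, the odds ratio is (6×148)/(60×6) = 2.47 and p is 0.19. The standard error of the log odds ratio is √(1/6 + 1/60 + 1/6 + 1/148) = 0.597. The approximate 95% interval is exp(0.903 ± 1.96×0.597) = 0.77 to 7.95.

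The verdict in the second case is *not significant*, yet the data are compatible with a nearly eightfold increase in odds. The interval shows that; the p-value does not.

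**The case against.** Several points on the other side stand.

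- **Low power is not itself an error.** The trial is sized for its primary outcome, and a secondary endpoint need not be powered.
- **The wording is hedged.** The endpoint concerns potential risk factors. The plan promises no independent predictors and nowhere says it will report non-significance as absence of risk. It also plans proportions with 95% intervals for categorical variables, intra-operative leak and tumour type among them. Those are descriptive, though, and do not give the association of a factor with failure.
- **The no-adjustment sentence is not tied to this endpoint.** It stands under additional analyses, in a paragraph on subsets that does not mention reconstruction failure, and it states an intention rather than a prohibition. The point survives because the main methods section gives secondary endpoints only univariable tests as well.
- **The Holm family is undefined.** A family of ten is inferred, so the 0.005 figures are illustrative.

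A reader might infer more than the text supports:

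- *That no plausible factor could be detected.* An odds ratio of 5 at 30% prevalence has 70% power at 0.05.
- *That the plan means to carry risk-factor results into practice.* The Discussion's sentence on future decision-making speaks of the trial's results generally and follows the non-inferiority aim.
- *That recurrence is linked to tumour size.* The Background does not mention recurrence.
- *That every model should adjust for intra-operative leak.* Leak may lie on the path from tumour size to failure, so forcing it in could hide the effect of size.

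**Conclusion.** The point holds as a minor improvement. The plan's own rates imply about 12 failures in 220 patients. For a factor present in 30% to 50% of patients, univariable tests then have about 13% to 18% power for an odds ratio of 2 and 29% to 40% for 3 at 0.05, and less at any stricter Holm step. The analysis as written would leave most factors of that size non-significant, give no effect estimate for their association with failure, and be unable to separate related ones.

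The event count follows from the Sample size section; the prevalences and odds ratios are assumed. The document does not support the stronger conclusion that the endpoint is worthless or that the trial's main conclusion is at risk: an unadjusted comparison of randomised arms is sound, and this point does not touch it.

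**What to change.** For this endpoint only:

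1. Label it exploratory.
2. Report for each factor, with intra-operative leak added to the list, the odds ratio for reconstruction failure and its 95% interval from Firth-penalised logistic regression, arms pooled, in place of a significance verdict.
3. State that a non-significant factor is not thereby shown to carry no risk.
4. Limit any model with more than one factor to one or two terms named before the outcome data are analysed, and present it as a sensitivity analysis. Do not force intra-operative leak into every model. Simply lifting the no-adjustment statement and fitting all the listed factors would not help, at about 1.2 failures per factor.
5. Confine the sentence that no adjusted analyses are intended to the analyses it is meant for.

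The cost is a change of analysis wording and a penalised regression in place of simple two-group tests, possibly in other software. No new patients or data are needed. The downside is wide intervals and a more modest claim.
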